#### Randomization, treatment allocation and blinding

After each individual OP has given their written informed consent for participating in the evaluation and has filled in the baseline questionnaire (T0), randomization will take place at the level of the existing peer groups. Participating groups of OPs will be randomly assigned to (1) the peer group supervision plan directed to the implementation of preventive tasks targeting work-related mental health problems (intervention groups) or (2) the usual peer group supervision condition (control groups). The control groups will be put on a waiting list and receive the peer group supervision materials after the 12 months follow-up of this study. To avoid bias, the randomization process will be executed by two independent researchers. Researcher 1 will assign consecutive numbers to each participating peer group. A computer-generated randomization will then be performed by researcher 2, in order to assign each number to either the intervention or control group. This way, allocation to either one of the groups cannot be influenced. Because of the intervention, blinding for allocation on the level of the participant (OP) is not possible.

#### Effect evaluation

##### Outcome measures

The primary outcome is the execution of preventive tasks aimed at the prevention of work-related mental health problems. This will be assessed by means of the self-reported number of hours spent on each of these tasks, and the self-reported percentage of time spent on prevention, absence and reintegration guidance, and other tasks (e.g. teaching responsibilities). Moreover, OPs will be asked if they would like to spend more time on prevention (ranging from “no, less time” to “yes, considerably more time”). If they want to spend more time on prevention, they will be additionally asked on what specific tasks (e.g. open consultation hour, advising about occupational health policy). Furthermore, questions derived from an existing questionnaire of the Netherlands Society of Occupational Medicine will be used [18]. This questionnaire consists of various statements concerning preventive tasks, whereby OPs must indicate to what extent the statement applies to their situation (ranging from “this applies to a very small degree” to “this always applies” and to what extent they consider it important (ranging from “very unimportant” to “very important”. A selection of 20 statements (out of 58 in the total questionnaire) will be included in the questionnaire. Examples of these statements are: *“I regularly visit the workplace to monitor the interaction between work and health and to evaluate opportunities and risks.”* or *“I give my employers solicited and unsolicited advice about preventive tasks, to prevent and limit health threats”* [18].

Secondary outcomes are the attitude, social influence and self-efficacy of OPs (ASE) [19]; perceived barriers for the execution of preventive tasks; and OPs’ experiences of their work. Their attitude, social influence and self-efficacy will be assessed with the Measurement Instrument for Determinants of Innovations (MIDI), developed by Fleuren et al. [20, 21]. The MIDI consists of 29 determinants, divided based on the different levels of implementation: the innovation, the user (i.e. the OP), the organizational context or the socio-political context [21]. Seven of these determinants will be included in the questionnaire to understand, for example, the degree to which OPs believe they are capable of using the intervention (“self-efficacy”). Perceived barriers will be assessed using the MIDI as well. Five determinants will be included: the formal ratification by the management, sufficient staff capacity, the availability of time, availability of financial resources and availability of material resources and facilities [21]. The first statement is dichotomous, with answer categories being yes and no. The other statements are categorical, with 5 answers ranging from “fully disagree” to “fully agree”. Finally, OPs’ own work experience, such as the work rate and quantity, variety in work and work satisfaction will be determined using the validated Dutch Questionnaire on the Experience and Evaluation of Work (QQEW; Dutch abbreviation: VBBA) [22]. All outcome measures will be determined at baseline, after 6 (T1) and after 12 (T2) months.

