#### Study population and recruitment

The study population consists of OPs and will be recruited in two steps. First, we will recruit peer group supervision groups via the Netherlands Society of Occupational Medicine. Second, we will recruit individual OPs within each participating peer group and ask whether they want to participate in the evaluation. Thus, an individual OP can decide not to participate in the evaluation, but could still participate in the specific prevention-oriented peer group supervision meetings. OPs will be excluded from participating in this evaluation when: (1) They have an upcoming retirement or long-term leave (e.g. pregnancy leave) during the follow-up of this study (i.e. 12 months), or (2) They work fewer than 16 h per week as an OP. The latter requirement is to ensure OPs have enough time available to focus on their preventive tasks and change something in their working habits.

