#### Sample size and power calculation

The sample size for this study was based on estimating an effect on the primary outcome, the self-reported percentage of time spent on preventive tasks. Using a one-sided Pearson’s chi-squared test of proportions at alpha = 0.05, assuming 0.1 and 0.25 of the total percentage of working hours per week being assigned to prevention tasks in the control and in the treatment groups, respectively, 80 participants were needed in each group to achieve a statistical power of 0.8. Considering a loss to follow-up of 20%, this study would require a sample size of 200 individual participants, of which half in the control and half in the intervention condition. Taking into account that each peer group consists of approximately eight people, this corresponds to approximately 25 peer groups. This analysis was done using the procedure power in SAS, version 9.4, and in consultation with an experienced statistician.

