##### Covariates

Data on potential confounders will be collected by questionnaire as well. These include both sociodemographic factors and organizational characteristics:

Individual characteristics of the OPs: age, number of working hours per week, number of years work experience, being self-employed.Organizational characteristics: sector, and if they are working for Small and Medium Enterprises (SME) or larger organizations.

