##### Data analysis

Data at baseline, 6 months (T1) and 12 months follow-up (T2) will be presented using descriptive statistics. To investigate the effectiveness of the intervention, differences between the intervention and control group in the outcomes at baseline, T1 and T2 will be analysed making use of longitudinal linear or logistic mixed models. If necessary, baseline differences between the intervention and control group will be adjusted for. Consistent with the design of the cluster-RCT and to avoid bias, analyses will be performed following the intention-to-treat principle. This means that all participants randomized will be kept in the groups they were randomized to, regardless of the intervention they received in practice [23]. For the analyses a two-tailed significance level of < 0.05 will be considered statistically significant. All statistical analyses will be performed with SPSS software, version 28.0.1.1.

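### Adjustment of the hours-per-task outcome for weekly working hours depends on observed imbalance; prespecifying it would give a small precision gain and remove a data-dependent choice

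*Protocol article*

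**What the plan says.** All references are to the protocol article.

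- **Outcome measures.** The primary outcome, execution of preventive tasks, is assessed by the "self-reported number of hours spent on each of these tasks" and by "the self-reported percentage of time spent on prevention, absence and reintegration guidance, and other tasks". The first is an absolute amount with no stated denominator. The second is already relative to working time, but for prevention as a whole, not task by task.
- **Study population and recruitment.** One ground for exclusion is "They work fewer than 16 h per week as an OP". No upper limit is given.
- **Covariates.** The individual characteristics collected as potential confounders are "age, number of working hours per week, number of years work experience, being self-employed".
- **Data analysis.** Outcomes at baseline, 6 and 12 months are analysed "making use of longitudinal linear or logistic mixed models". The only rule on covariates is: "If necessary, baseline differences between the intervention and control group will be adjusted for".
- **Sample size and power calculation.** The trial is sized on "the primary outcome, the self-reported percentage of time spent on preventive tasks", not on hours.

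**The concern.** An OP working 16 h a week and one working 40 h can give prevention the same share of their time and report very different hours. With the shares assumed in the sample size section, 0.25 × 16 = 4.0 h for a 16 h OP at the intervention value, and 0.10 × 40 = 4.0 h for a 40 h OP at the control value (the 40 h is an assumption). Working time therefore predicts the hours outcome, and it is measured before randomisation.

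A baseline variable that predicts the outcome improves precision whether or not the arms happen to differ on it. The written rule ties adjustment to observed differences between arms. That has two consequences for the hours measure: the predictor is left out by default, and the model is settled only after the baseline data have been compared, on a criterion the article does not define. At stake are a little precision and one analytic choice that could be fixed in advance, for one component of the primary outcome.

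**Working it through.** **1. The plan's own figure.** Shares of 0.10 and 0.25, with the test described as "Using a one-sided Pearson’s chi-squared test of proportions at alpha = 0.05", and power 0.8 give 79 per arm (pooled variance, no continuity correction), against the stated 80. Then 80 / 0.8 = 100 per arm, 200 in total, and 200 / 8 = 25 groups. The stated size reproduces. It rests on the percentage, so nothing below changes it.

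**2. Assumed inputs.** The documents give no distribution of hours. Assume:
- weekly hours W uniform from 16 to 40: mean 28, variance 24²/12 = 48, E[W²] = 28² + 48 = 832;
- prevention share p independent of W, with mean μ and CV c of 0.33, 0.67 or 1.0;
- correlation ρ = 0.6 between the baseline and follow-up share;
- no clustering.

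Hours are H = W × p.

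**3. Formulas, in units of μ².**
- Variance of hours: V = 832c² + 48. The 48 is the part due to working time.
- After linear adjustment for W only: 832c².
- After adjustment for baseline hours only: V(1 − r²), with r = (832ρc² + 48) / V.
- After adjustment for baseline hours and W: 832c²(1 − ρ²).

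**4. Results with baseline hours in the model (ρ = 0.6).** The last column starts from 80% two-sided power without W and multiplies 1.960 + 0.842 by the square root of the variance ratio.

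| c | V | r | Baseline only | Baseline + W | Ratio | Power |
|---|---|---|---|---|---|---|
| 0.33 | 138.6 | 0.739 | 63.0 | 58.0 | 1.087 | 0.80 → 0.83 |
| 0.67 | 421.5 | 0.646 | 245.8 | 239.0 | 1.028 | 0.80 → 0.81 |
| 1.0 | 880.0 | 0.622 | 539.7 | 532.5 | 1.014 | 0.80 → 0.81 |

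The gain is about 0.5 to 3 points. A simulation with 80 per arm under the same assumptions agrees: 0.92 to 0.93 at c about 0.67, and 0.90 to 0.92 at c about 0.33.

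**5. Change from baseline.** H1 − H0 = W(p1 − p0). Without a treatment effect the bracket has mean zero, so the change is uncorrelated with W and adjustment gains essentially nothing.

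**6. Baseline not used.** The ratio is V / 832c²: 138.6 / 90.6 = 1.53 at c = 0.33, and 880 / 832 = 1.06 at c = 1.0. With the effect set so that the percentage measure has 80% power, power for hours rises from 0.59 to 0.78 at c = 0.33 and from 0.75 to 0.78 at c = 1.0, a gain of about 2 to 18 points.

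**7. Sensitivity to ρ.** At c = 0.33, ρ = 0.4 gives 87.4 / 76.1 = 1.148 (0.80 → 0.85) and ρ = 0.8 gives 33.9 / 32.6 = 1.04 (0.80 → 0.81). The 0 to 3 point range therefore depends on a baseline correlation of about 0.6 or higher.

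**The case against.** The strongest reply is that this is an efficiency preference raised against a condensed article, and much of that reply stands.

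- **Silence on scaling.** A reader might infer that hours will be analysed unscaled. The article does not say so. It says what is asked and names a model family; how each component is derived may be left to the analysis plan. That inference is not made here.
- **A scaled measure exists.** The percentage of time is already relative to working time and is what the trial was sized on. Absolute hours answer a different and legitimate question, how much prevention is delivered. Re-expressing total hours as a percentage would largely duplicate the existing measure, so it is not proposed.
- **Imbalance is covered.** If the arms differ in working hours, the conditional rule is meant to apply, and chance imbalance under randomisation is not bias. This is correct. What remains is the case where the arms look similar, and the undefined criterion for deciding.
- **Size.** Raw hours at a single time point have 1.12 to 1.31 times the relative variance of scaled hours (share CV 1.0 down to 0.5), and a reader might take this as losing 11% to 23% of the sample. That does not fit this plan. It describes dividing by working hours with no baseline value, whereas outcomes are measured at baseline and the models are longitudinal. It is also not the gain from an additive covariate.

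The objection does not dispose of the adjustment rule itself. That rule is stated, not omitted, and it makes use of a known predictor conditional on the data.

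**Conclusion.** The point holds as a minor one. For the hours-per-task component, the stated rule by default leaves out a predictor that is already collected, and it makes the model depend on the observed baseline comparison. Prespecifying the covariate gains about 0 to 3 points of power when the baseline outcome is in the model, essentially none if the contrast is change from baseline, and about 2 to 18 points only if baseline is not used.

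These figures rest on assumptions the documents do not supply: 16 to 40 h uniform, working time independent of the prevention share, share CV 0.33 to 1.0, baseline correlation 0.6, no clustering. A baseline correlation of 0.4 raises the upper end to about 5 points. If shares for single tasks vary more than the total, the gain shrinks further.

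The documents do not support reading this as a bias in the randomised comparison. The percentage-of-time measure and the 80 per arm are untouched.

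**What to change.** In the Data analysis section, state that the models for hours spent on preventive tasks include baseline weekly working hours as a fixed covariate, together with the baseline value of the outcome, whether or not the arms differ at baseline. The conditional rule then no longer governs this variable for these models.

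The cost is one sentence and one degree of freedom per model. No new data are needed, because working hours are already in the questionnaire, and the sample size does not change. The sentence should be fixed before the baseline data are compared by arm.

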### Step 2 – implementation outcomes, performance objectives, determinants and change objectives

An example of a matrix of change objectives for OPs, including the behavioural outcomes, performance objectives and personal determinants, can be found in Table 2. In this matrix, the behavioural outcome is OPs having sufficient knowledge, skills and interest to carry out their preventive tasks, and to show initiative to put prevention on the agenda of the organization. Related determinants are knowledge, self-efficacy and outcome expectations.

**Table 2 Tab2:** Matrices of change objectives for occupational physicians, describing the key actor and main goal, tasks required to reach the goal, determinants influencing these tasks (i.e. barriers) and required changes

Behavioural outcome	Performance objective	Personal determinant	Change objectives
OP has sufficient knowledge, skills and interest to carry out preventive tasks and shows initiative and perseverance to put prevention on the agenda within a company	OP integrates the execution of preventive tasks in their other work	Knowledge	Knowledge is shared among OPs through e.g. their own network, magazines, and the professional association.
		Self-efficacy	OP expresses confidence in the ability to use existing materials and protocols in the execution of preventive tasks.

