### Step 5 – evaluation plan

#### Study design

To evaluate the implementation of the developed intervention, a two-armed cluster randomized controlled trial (RCT) will be conducted. The design of a cluster-RCT has been chosen, because the intervention will be delivered at a group level [16]. The OPs in the groups randomized to the intervention will participate in peer group supervision directed to implementation of preventive tasks targeting work-related mental health problems in their current practice. Groups of OPs randomized to the control condition will not get (initial) access to the intervention and materials. They will be put on a waiting list and participate in their peer group supervision as usual. The evaluation will consist of an effect evaluation and process evaluation. Each individual OP in both the intervention and control group will be asked to complete an online questionnaire at baseline (T0), after 6 months (T1) and after 12 months (T2). In addition, interviews will be held with a selection of participating OPs.

This study will be performed in accordance with the ethical guidelines and regulations laid down in the Declaration of Helsinki. Moreover, this study will be reported in adherence with the CONSORT Guidelines [17]. This study was approved by the Medical Ethics Review Committee of the Academic Medical Center Amsterdam, the Netherlands. The Medical Research Involving Human Subjects Act (WMO) does not apply to the above mentioned study. Written informed consent will be obtained via an online registration form from all participants prior to participating in this study.

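### Self-efficacy is described as confidence in using the intervention, which controls and pre-randomisation respondents have not received, yet it is compared between arms from baseline to 12 months

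*Protocol article*

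**What the plan says.** All references are to the protocol article.

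- **What is measured.** Outcome measures lists attitude, social influence and self-efficacy as secondary outcomes of the effect evaluation, assessed with seven MIDI determinants. Self-efficacy is the example given, described as "the degree to which OPs believe they are capable of using the intervention".
- **When.** "All outcome measures will be determined at baseline, after 6 (T1) and after 12 (T2) months".
- **By whom.** Study design has every participating OP in both arms complete the online questionnaire.
- **Baseline before allocation.** Randomization, treatment allocation and blinding says that once each OP has consented and "has filled in the baseline questionnaire (T0), randomization will take place at the level of the existing peer groups".
- **Control access.** Study design: "Groups of OPs randomized to the control condition will not get (initial) access to the intervention and materials". The randomisation section adds that control groups "receive the peer group supervision materials after the 12 months follow-up of this study".
- **Analysis.** Data analysis compares the arms at baseline, T1 and T2 with longitudinal mixed models.
- **Self-efficacy elsewhere.** Table 2 (Step 2 of the development results) gives the self-efficacy change objective as: "OP expresses confidence in the ability to use existing materials and protocols in the execution of preventive tasks".

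**The concern.** The described object of the self-efficacy measure does not fit the measurement schedule or the control condition. At baseline no one has attended the intervention meetings. Controls have still not attended them at 6 or 12 months. An OP asked how capable they feel of using something they have not received can only guess, skip the question, or answer about something else.

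The first research question asks for effects on the behavioural determinants of OPs, and self-efficacy is a named component. If the item followed the description, change from baseline in the intervention arm would run from a hypothetical rating to an experienced one. The contrast with controls would set experienced ratings against hypothetical ones. Either could move because OPs had met the intervention, without any change in their confidence to do preventive work. No later analysis could separate the two, because the object of a questionnaire item is fixed once the answers are in.

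**Working it through.** **1. The plan's own numbers.** Sample size and power calculation states 80 OPs per group, 20% loss to follow-up and 200 OPs in total. This reproduces: 80 / (1 − 0.20) = 100 per arm, and 2 × 100 = 200. These figures serve only to count responses here; the point does not depend on them.

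**2. Planned self-efficacy responses.** 2 arms × 3 times = 6 cells. With 100 OPs per cell before loss to follow-up, that is 6 × 100 = 600 responses.

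**3. Has the respondent received the intervention by then?**

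| Arm | T0 | T1 (6 months) | T2 (12 months) |
|---|---|---|---|
| Intervention | No: T0 precedes randomisation | Yes: three meetings within six months | Yes |
| Control | No: T0 precedes randomisation | No: waiting list | No: materials come after the 12-month follow-up |

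Cells with something to rate: 2 of 6, or 2 × 100 = 200 of 600 responses. Cells without: 4 of 6, or 400 of 600. The 200 is an upper figure, because it counts every OP in an intervention group as having attended by T1.

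**4. What the article means by the intervention.** The Abstract (Results) says it consists of three peer group supervision meetings. Study design withholds it from controls, who go on practising as OPs. In both places it is something other than preventive tasks, which OPs in either arm can carry out.

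**5. The three descriptions side by side.**

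| Place | Object | Rateable by both arms at T0, T1 and T2? |
|---|---|---|
| Outcome measures, self-efficacy | Using the intervention | No |
| Table 2, self-efficacy | Existing materials and protocols, used in preventive tasks | Yes |
| Outcome measures, perceived barriers (five MIDI determinants) | Execution of preventive tasks | Yes |

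The first row stands apart. The third comes from the same section and the same instrument, so an object that fits both arms was already in use there.

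**The case against.** The best case on the other side is that the clause is a one-line illustration introduced with *for example*. It is neither a definition nor the item text. The questionnaire is not shown, and a journal article commonly leaves item wording to fuller documents. Most of the article treats preventive tasks as the thing being implemented: the study aim, the barrier review, Table 2 and the MIDI barrier outcome all point that way. On that reading, the reference to the intervention is loose wording for preventive tasks, and the actual item may already suit both arms.

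Much of this stands. A reader might infer that self-efficacy is formally defined this way, so that no valid baseline or control value will exist. The article does not support that, because it does not give the item. A reader might also infer that attitude and social influence share the fault. Nothing says what the other six determinants refer to. Nor does the article lack a place for questions about the intervention: Process evaluation already plans a questionnaire covering acceptability, adoption, feasibility and fidelity, among other indicators.

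The objection does not remove the mismatch. The benign reading is possible but not stated, and the article elsewhere uses the word for the peer group meetings. This clause is also its only account of what self-efficacy measures as a trial outcome. The point concerns what the article states, not what it leaves out.

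**Conclusion.** The point holds as an inconsistency in how one secondary outcome is described. Followed as written, the self-efficacy item could be answered from experience in 2 of 6 arm-by-time cells, at most about 200 of 600 planned responses. Neither the arm difference nor the change from baseline could then be read as an effect on self-efficacy for prevention. The description also has to be reconciled with Table 2 and with the barrier outcome.

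The count assumes 100 OPs per arm, no loss to follow-up, attendance by all intervention OPs before T1, and no access for controls before T2. The conclusion is conditional on the item following the description; if the item already refers to preventive tasks, only the article's wording needs correcting. Self-efficacy is the only determinant shown to be affected. The primary outcome, the sample size and the randomisation are untouched. The change is worth making because it is nearly free and decides whether this outcome can be interpreted.

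**What to change.** - Word the self-efficacy item around carrying out preventive tasks for work-related mental health problems, identically in both arms at T0, T1 and T2. Do the same for any other of the seven MIDI determinants that refers to the intervention.
- Correct the description in Outcome measures so that it agrees with Table 2 and with the barrier outcome.
- Put any question about using the intervention itself in the process questionnaire already planned, for the intervention arm only.
- The article does not say whether T0 has been sent. If it has been fielded with intervention-specific wording, report that wording and do not interpret the between-arm difference as an effect on self-efficacy for prevention.

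Before T0 the cost is a change of wording, with no added burden on respondents and no effect on sample size or timeline. After T0 the cost is a limit on what can be claimed for this one outcome.
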